### Study follow-up and data collection

The primary and the secondary outcomes will be assessed at all follow-up visits (Table 2). Baseline patient characteristics and outcome data (over time) are collected in an online electronic case report form (eCRF). The eCRF that will be used is KLIK (Dutch acronym for Quality of Life in Clinical Practice [12]) (www.hetklikt.nu). KLIK is an online PROM tool made for children and accessible for patients and clinicians during consultation to evaluate any sense of alarm according to the clinical criteria or concern of the patient/parent.

### Sample size

The sample size is based on identifying superiority of the PE-FU in each individual RCT. The 3 subgroups for this study differ in nature; this means that separate sample size calculations are required. An unpublished survey of Dutch patients with AIS showed that 50% of patients had a preference for 1 of the 2 cohorts (the preference cohorts) and 50% were willing to participate in the RCT, which is comparable to an American study that used a similar design [13]. By doubling the sample size needed for the RCTs, the total sample size is achieved. As no previous studies regarding this subject are available, the literature was searched for patient samples with AIS that resemble the study population and that showed progression of the curve during natural history [14] or after surgery [15]. Assumptions were made based on the literature and expert opinion. Typically, patients with AIS and their parents/caregivers are very compliant with follow-up. A 10% dropout or lost-to-follow-up for the 3 subgroups is expected. Based on the above, for this study a total of 812 patiens is required (alpha 0.05; beta 0.80). This means for the RCT: 66 per arm for pre-treatment, 61 per arm for post-brace, and 76 per arm for post-surgery (subtotal of patients in RCT is 406) (Figure 1) (for a detailed explanation, see Appendix 1).

### Data analysis

Primary analyses will be performed according to intention to treat (ITT) principle. Analyses will be performed with R in R Studio (version 2022.2.1.461; R Foundation for Statistical Computing, Vienna, Austria) and uses P < 0.05 to indicate statistical significance.

#### Effect evaluation primary outcome parameter

To evaluate the difference in clinical effectiveness of both follow-up protocols, the number of radiographs with treatment consequences will be divided by the total number of radiographs in each subgroup (pre-treatment, post-brace, post-surgery). To compare the primary outcome between the PE-FU group and the S-FU group, Pearson’s chi-square test is used. To evaluate the effect according to subgroups, linear mixed-effects models that account for repeated measurements will be performed, adjusted for scoliosis center and relevant baseline covariates. Assumptions of linear mixed modelling will be assessed and if needed variable transformations will be performed. Furthermore, for each subgroup the results of the RCT follow-up protocols will be compared with the similar preference cohort to indicate generalizability of study results.

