**Methods and analyses:**

A nationwide multicenter pragmatic randomized preference trial was designed for 3 follow-up subgroups (pre-treatment, post-brace, post-surgery) to compare PE-FU and S-FU. 812 patients with AIS (age 10–18 years) will be included in the randomized trial or preference cohorts. Primary outcome is the proportion of radiographs with a treatment consequence for each subgroup. Secondary outcomes consist of the proportion of patients with delayed initiation of treatment due to non-routine radiographic follow-up, radiation exposure, societal costs, positive predictive value, and interrelation of clinical assessment, quality of life, and parameters for initiation of treatment during follow-up. Outcomes will be analyzed using linear mixed-effects models, adjusted for relevant baseline covariates, and are based on intention-to-treat principle. Study summary: (i) a national, multicenter pragmatic randomized trial addressing the optimal frequency of radiographic follow-up in patients with AIS; (ii) first study that includes patient-empowered follow-up; (iii) an inclusive study with 3 follow-up subgroups and few exclusion criteria representative for clinical reality; (iv) preference cohorts alongside to amplify generalizability; (v) first study conducting an economic evaluation comparing both follow-up approaches.

Adolescent idiopathic scoliosis (AIS) is a 3-dimensional deformity of the spine and trunk in adolescents that occurs in 2–3% of healthy children [1]. Because severe curves have a negative impact on quality of life in adulthood, patients with AIS are regularly seen for radiographic follow-up to detect curve progression, so that timely treatment can be initiated [2]. Treatment consists of thoracolumbar orthosis (brace) or surgery. The length and intensity of radiographic follow-up after treatment varies widely among physicians and lack of consensus exists on the need for long-term radiographic follow-up.

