The current standard of care is based on regular radiographic follow-up as recommended in national and international consensus papers [3-5]. Regular radiographic follow-up leads to multiple radiographs without consequences for individual patient treatment. The developing tissues of adolescent patients are exposed to ionizing radiation, which previously has been associated with an increase in risk of breast and endometrial cancer [6,7]. Although technological advances have reduced the radiation dose tremendously, lack of evidence to support routine radiographic follow-up still warrants investigation of new protocols [8,9]. Additionally, a reduction of radiographs reduces the financial burden on the healthcare system. To optimize follow-up protocols of patients with AIS, an AIS Consortium including Dutch scoliosis treatment centers was established to evaluate a new patient-empowered follow-up protocol.

The purpose of this nationwide study is to evaluate whether a reduction in the number of radiographs can be achieved without negative consequences for individual treatment of patients with AIS, by combining clinical measurements and empowering patients through education and self-management.

The hypothesis is that the patient-empowered follow-up-protocol results in a (cost-)effective and safe reduction of the number of radiographs.

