### Study interventions

#### Patient-empowered follow-up (PE-FU) protocol (Figure 2)

The PE-FU protocol consists of patient-reported outcome measures (PROMs), the Scolioscope and clinical assessment including physical examination by the physician. The Scolioscope is a self-assessment tool that measures the trunk rotation, similar to what is measured with the Bunnell scoliometer (Figure 3). At baseline and at last follow-up (24 months) biplanar radiographs are taken. Instead of routine radiographs, at all intervening follow-up visits radiographs will only be taken when curve progression or postoperative complications are suspected based on so-called “sense of alarm” criteria, which is a signal for the treating physician to consider whether a radiograph is appropriate.

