### Patient characteristics and outcome measures (Table 2)

At baseline, relevant patient characteristics are collected to describe the study sample, including the 3 different subgroups. Primary outcome is defined as the proportion of radiographs that has led to treatment consequences in each subgroup (pre-treatment, post-brace, post-surgery). A treatment consequence is defined as start of brace therapy or any surgical intervention. Secondary outcome measures include both patient and clinician-reported outcomes.

**Table 2 T0002:** Baseline characteristics, secondary outcome measures, and measurement moments

Variable	Month of follow-up assessments					
	Baseline	3	6	12	18	24
Post-surgery group	√	√	–	√	–	√
Pre-treatment group and post-brace group	√	–	√	√	√	√

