### Explanation of the sample size calculation per subgroup

#### Pre-treatment group

In the literature, a 23% risk of curve progression was described [25] (i.e., comparator; usual/S-FU care). In the pre-treatment group, routine follow-up takes place every 6 months for a duration of 24 months (i.e., 4 follow-up assessments). Consequently, the incidence of progression per radiograph is 5.75% (i.e., 23%/4) for the control group/S-FU group. Based on the literature and expert opinion, a 5% margin is allowed for the PE-FU and 20% extra radiographs are expected for this group. The margin of 5% results in 28% risk of curve progression for the investigational group/PE-FU group (23% + 5% = 28%). Therefore, the incidence of progression per radiograph is expected to be 23.3% (i.e., 28%/1.20) for the PE-FU group (intervention/investigational group). For the increase in incidence/radiograph from 5.75% to 23.3%, the calculated sample size is 60 patients per arm (given a 95% CI and 80% power). Taking into account the expected loss to follow-up/dropout (10%), the final sample size is 66 patients for each treatment arm in the pre-treatment group.

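### The primary outcome measures yield per radiograph and can favour PE-FU even when many treatment starts are missed, so it cannot support the word safe, and no two-arm criterion for missed or late treatment is stated

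*Protocol article*

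**What the plan says.** The introduction of the protocol article hypothesises that PE-FU "results in a (cost-)effective and safe reduction of the number of radiographs". The primary outcome is offered as the measure of clinical effectiveness: "the number of radiographs with treatment consequences will be divided by the total number of radiographs in each subgroup" (Effect evaluation primary outcome parameter). For the comparison of arms, "Pearson’s chi-square test is used". The numerator event has no timing element: "A treatment consequence is defined as start of brace therapy or any surgical intervention" (Patient characteristics and outcome measures).

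The direction of the test is fixed: "The sample size is based on identifying superiority of the PE-FU in each individual RCT" (Sample size). In PE-FU, radiographs are scheduled at baseline and month 24, and "at all intervening follow-up visits radiographs will only be taken when curve progression or postoperative complications are suspected".

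The Appendix adds five percentage points to the PE-FU risk in each subgroup. For the pre-treatment group it says: "Based on the literature and expert opinion, a 5% margin is allowed for the PE-FU". The abstract lists one secondary outcome aimed at late treatment: "the proportion of patients with delayed initiation of treatment due to non-routine radiographic follow-up".

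**The concern.** The strategy under test largely sets the denominator of the primary outcome. PE-FU drops the routine radiographs between baseline and month 24, so its ratio can rise without any gain in detection and can stay higher despite a loss of detection. Three features add to this.

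- Progression first found on the month-24 radiograph counts the same as progression found at six months.
- The extra five points of progression allowed for PE-FU enter its numerator. They widen the contrast in favour of PE-FU, and nothing tests them as a limit.
- The outcome directed at late treatment is worded as a result of non-routine follow-up. S-FU patients have a routine radiograph at every visit, so, read literally, the outcome has no counterpart in that arm.

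The Discussion acknowledges that detection, and so treatment, might be delayed in the pre-treatment and post-brace subgroups. It also expects the results to inform guidelines. A significant primary result could then be cited as proof of a safe reduction that the test never examined.

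**Working it through.** **Inputs** (Appendix, sample size per subgroup)

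| | Pre-treatment | Post-brace | Post-surgery |
|---|---|---|---|
| S-FU patient risk | 23% | 23% | 10% |
| S-FU follow-up radiographs per patient | 4 | 4 | 6 (films) |
| PE-FU patient risk (S-FU + 5 points) | 28% | 28% | 15% |
| PE-FU radiographs per patient | 1.20 | 1.15 | 1.05 |
| n per arm before dropout | 60 | 55 | 69 |

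**1. The plan's own figures reproduce.** The formula is n = (1.96 + 0.8416)² × [p1(1−p1) + p2(1−p2)] / (p1−p2)², two-sided 0.05, 80% power.

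- Pre-treatment, 5.75% v 23.3%: 59.4, rounded up to 60.
- Post-brace, 5.75% v 24.3%: 54.3, rounded up to 55.
- Post-surgery, 1.7% v 14.3%: 68.8, rounded up to 69.

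Multiplying by 1.10 gives 66, 61 and 76. Then 2 × (66 + 61 + 76) = 406, and doubling gives 812.

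**2. Where the planned contrast comes from.** The ratio PE-FU/S-FU equals (risk ratio) × (S-FU radiographs / PE-FU radiographs).

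- Pre-treatment: (28/23) × (4/1.20) = 1.22 × 3.33 = 4.1.
- Post-brace: (28/23) × (4/1.15) = 1.22 × 3.48 = 4.2.
- Post-surgery: (15/10) × (6/1.05) = 1.50 × 5.71 = 8.6.

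The second factor is the reduction in radiographs. The first is the five-point allowance for extra progression. Neither is better detection.

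**3. Equal detection and break-even.** With equal patient risk, the PE-FU ratio is 23%/1.20 = 19.2%, 23%/1.15 = 20.0% and 10%/1.05 = 9.5%, against 5.75%, 5.75% and 1.7% in S-FU. The arms tie when the PE-FU patient proportion equals the S-FU ratio times the PE-FU radiographs per patient.

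- Pre-treatment: 5.75% × 1.20 = 6.9%, so 1 − 6.9/23 = 70% missed.
- Post-brace: 5.75% × 1.15 = 6.6%, so 71% missed.
- Post-surgery: (10%/6) × 1.05 = 1.75%, so 82.5% missed.

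The post-surgery figures count six films in S-FU but about one radiograph in PE-FU, although the month-24 PE-FU radiograph is biplanar. Counting visits in both arms (3 v 1.05) or films in both (6 v 2.1) gives a tie at 3.5%, so 65% missed.

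**4. Chance of declaring PE-FU superior when treatment starts are missed.** This is the two-proportion normal approximation at the planned n. The article does not say what the unit of the chi-square test is, so both are shown.

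| Missed in PE-FU | Unit | Pre-treatment | Post-brace | Post-surgery |
|---|---|---|---|---|
| None | radiographs | 89% | 88% | 86% |
| None | patients | 61% | 61% | 52% |
| A quarter | radiographs | 64% | 64% | 70% |
| A quarter | patients | 35% | 35% | 35% |
| Half | radiographs | 24% | 25% | 42% |
| Half | patients | 12% | 13% | 18% |

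Simulating the pre-treatment RCT (60 per arm, 240 v 72 radiographs) gives 91% with none missed, 63–64% with a quarter missed and 22% with half missed. With post-surgery radiographs counted alike (3 v 1.05), the radiograph-unit figures fall to 54%, 31% and 10%.

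**5. Precision of a patient-level comparison.** The 95% CI half-width is 1.96 × √[2p(1−p)/n].

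- p = 0.23, n = 60: 15.1 points.
- p = 0.23, n = 55: 15.7 points.
- p = 0.10, n = 69: 10.0 points.

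**The case against.** Yield per radiograph is a legitimate primary outcome for a trial prompted by radiographs that change nothing. That stands, and it is why the ratio need not be replaced. Several stronger readings that a reader might infer are not supported.

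- *The ratio rises automatically.* It does not. It favours PE-FU only while radiographs fall proportionally more than treatment starts, and past the break-even in step 3 it favours S-FU.
- *There is only one safety outcome, so the trial can say nothing about safety.* Table 2 also lists adverse events, Cobb progression and PROMs, secondary outcomes are compared per subgroup, and both arms have biplanar radiographs at month 24. What is lacking is a stated between-arm criterion for missed or late treatment.
- *Progression in PE-FU is unobserved until month 24.* Only its radiographic timing is. Patients attend for clinical examination, with scoliometer and Scolioscope readings and alarm thresholds.
- *The planned 0.20, 0.15 and 0.05 extra radiographs cap detection before month 24.* They are expert-opinion planning inputs. Any concern may trigger a radiograph, so they do not predict conduct.
- *The delay outcome is a proven structural zero in S-FU.* The wording appears in the abstract only, and the full protocol may define it neutrally.
- *The five points are a non-inferiority margin.* The Appendix uses them as a planning allowance. As a margin (one-sided 0.025, equal true risk) they would give about 9–16% power at the planned sizes, and 80% power would need about 1,113 per arm at 23% or 566 at 10%.

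**Conclusion.** The concern holds in limited form. As defined and tested, the primary outcome cannot support the safety part of the hypothesis or a claim of clinical superiority. On the plan's inputs it favours PE-FU until roughly 70% (pre-treatment), 71% (post-brace) and 65–82.5% (post-surgery) of treatment starts are missed. With a quarter missed in the pre-treatment RCT, superiority is still declared in about 35% of trials (patients as the unit) to 63% (radiographs as the unit).

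These sizes rest on the Appendix's risks and radiograph counts and, for the radiograph unit, on treating radiographs as independent. The direction of the problem depends on neither: the ratio carries no information on timing, and it credits extra progression to PE-FU. The comparisons that do bear on safety are listed, but the article gives no criterion for missed or late treatment that applies to both arms.

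**What to change.** 1. Keep the ratio, but state that it is interpreted as yield per radiograph and not as evidence of safety or clinical superiority.
2. Define delayed or missed treatment in identical terms for both arms, using the month-24 radiographs that both already have. The trial team should set a definition suited to each subgroup, including post-surgery, where the planning event is adding-on. The article states no Cobb threshold for treatment that could simply be borrowed.
3. Report radiographs per patient, the proportion of patients treated and the proportion delayed or missed, per subgroup, as randomised comparisons with 95% CIs.
4. State in advance the half-widths from step 5 of the working, so that a non-significant difference is not read as safety. If the team wants a margin, it must justify one. The five-point planning allowance should not be adopted by default.

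The cost is a change of wording and a little more analysis of data already collected. The downside is that the trial will probably be unable to claim safety in any single subgroup.

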## Methods and analysis

### Study design and setting

A multicenter pragmatic trial, a partially randomized preference trial (PRPT), will be performed in The Netherlands. Dutch scoliosis treatment centers were asked to participate in this study. The PRPT consists of 3 separate randomized controlled trials (RCTs), including patients with AIS who are followed in the pre-treatment, post-brace, or postoperative phase (i.e., subgroups). Alongside the RCTs, prospective patient preference cohorts are included for each follow-up subgroup. In these cohorts, all patients are monitored who are not willing to be randomized to either follow-up arm, but who are still willing to participate in the study and who prefer either follow-up protocol. The follow-up period is 24 months per patient. A flow of the study progress following the CONSORT statement [10] is provided in Figure 1. The study will be reported according to CONSORT guidelines.

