#### Standard follow-up (S-FU) protocol (Figure 2)

The S-FU protocol consists of routine full spine radiographs taken at inclusion and each follow-up visit, to detect possible curve progression or to rule out postoperative complications. For the post-surgical group, biplanar (posterior-anterior [PA] and lateral) radiographs are taken at each follow-up assessment. For pre-treatment and post-brace groups uniplanar radiographs are taken, with biplanar radiographs at baseline and at last follow-up (24 months) visit.

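### The primary denominator does not stop at a patient's first treatment consequence, so the ratio mixes surveillance yield with later imaging and, within PE-FU, falls when progression is found earlier

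*Protocol article*

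**What the plan says.** Under Effect evaluation primary outcome parameter, the count of radiographs that had a treatment consequence "will be divided by the total number of radiographs in each subgroup". Under Patient characteristics and outcome measures, "A treatment consequence is defined as start of brace therapy or any surgical intervention".

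Nothing ends the count when such a consequence occurs. Under Study design and setting, "The follow-up period is 24 months per patient"; Study follow-up and data collection has the primary outcome assessed at every follow-up visit; and under Data analysis, "Primary analyses will be performed according to intention to treat (ITT) principle".

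The film schedules make no exception for patients already treated. "The S-FU protocol consists of routine full spine radiographs taken at inclusion and each follow-up visit". PE-FU has films at baseline and month 24, and in between only on a sense of alarm.

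The appendix fits a count that runs to month 24. For the pre-treatment and post-brace groups it divides the 23% risk by all four follow-up assessments, progressors included.

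**The concern.** Each RCT concerns one phase of care, "including patients with AIS who are followed in the pre-treatment, post-brace, or postoperative phase". A pre-treatment or post-brace patient leaves that phase when a brace is started or surgery is done. Table 1 draws the same line at entry: patients under brace treatment are excluded, and post-brace patients enter only after bracing has ended. A patient who starts a brace during the trial is nevertheless still counted, film by film.

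A film taken after treatment has begun says little about whether surveillance films change treatment, yet it lowers the ratio. The sample size section treats a higher ratio in PE-FU as superiority. For a given number of progressors and no false alarms, the highest PE-FU value then belongs to an arm that finds every one of them only at month 24. The Discussion (Strengths) names late detection as the potential risk in the pre-treatment and post-brace groups, and the Abstract lists delayed treatment as a secondary outcome. The primary ratio pulls against both.

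**Working it through.** **Inputs (pre-treatment, Appendix).** S-FU: 23 progressors per 100 patients and 4 follow-up assessments. PE-FU: 28 progressors per 100 and 120 films per 100, that is, the month-24 film for everyone plus 20 extra. As in the appendix, baseline films are left out and each assessment counts as one film. I take treated patients to stay on their arm's documented schedule, with no added films.

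**Reproducing the plan.** S-FU 23/400 = 5.75%. PE-FU 28/120 = 23.3%. With n = (1.96 + 0.8416)² × [p1(1−p1) + p2(1−p2)] / (p1−p2)², these give 60 per arm, as stated.

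**PE-FU, all films counted, no false alarms.** Each early detection adds one alarm film, and the month-24 film remains. If a share k of the 28 is found early, the ratio is 28/(100 + 28k).

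| Found before month 24 | Films | Ratio |
|---|---|---|
| none | 100 | 28.0% |
| half | 114 | 24.6% |
| all | 128 | 21.9% |

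Against 5.75%, the plan's formula gives 41 per arm at 28.0% and 68 at 21.9%. Detection time alone moves the requirement across the stated 60.

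**PE-FU at the planned 120 films.** Two opposite cases:

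- All 20 extra films are true early detections. All films: 28/120 = 23.3%. Stopped at the treatment-leading film: 20 patients contribute one alarm film each and 80 contribute their month-24 film, so 28/100 = 28.0%.
- All 20 extra films are false alarms. Nobody stops early, so both counts give 28/120 = 23.3%.

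The all-films ratio cannot tell the two cases apart; the stopped ratio can.

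**S-FU.** With all films counted on the fixed schedule, the ratio is 23/400 = 5.75% at any detection time. Stopped at visit v, it is 23/(77 × 4 + 23 × v):

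| Detection | Films | Stopped ratio |
|---|---|---|
| month 6 | 331 | 6.95% |
| month 12 | 354 | 6.50% |
| month 18 | 377 | 6.10% |
| month 24 | 400 | 5.75% |
| spread evenly | 365.5 | 6.29% |

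With 6.29% against 28.0%, the plan's formula gives 44 per arm.

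**Other subgroups, on the appendix's own counts.** If all extra PE-FU films are true detections, post-brace goes from 28/115 = 24.3% to 28/100 = 28.0%. Post-surgery goes from 15/105 = 14.3% to 15/100 = 15.0%. Post-surgery S-FU goes from 10/600 = 1.67% to at most 10/(90 × 6 + 10 × 2) = 1.79%. The effect is smaller there.

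**The case against.** The article condenses a fuller protocol, and counting windows are often left to the SAP. No text describes imaging after treatment starts or says outright that those films count. That limits how far the point can go, but it does not remove it. The article states a denominator, and its sample size arithmetic uses the same count. If another document contains a cut-off, this section needs to be aligned with it.

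A reader might infer that any arm which detects progression earlier scores lower. The documents do not support that for S-FU: on its fixed schedule the ratio is 5.75% at every detection time. What S-FU loses is the rise that an at-risk count would show.

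A reader might also picture brace checks and perioperative films pulling the ratios much further down, for example PE-FU to 28/(120 + 20 × 4) = 14.0%. That needs four further films for each of 20 patients, and the documents mention no such films. At the planned 120 films, which already include month 24 for everyone, timing alone does not change 23.3%.

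Stopping the count has faults of its own. The denominator then depends on the outcome, and the S-FU ratio then varies with timing. A second consequence, such as surgery after a brace, also leaves the primary count. These are fair points. But the S-FU variation runs in the sensible direction, since earlier detection raises the yield, and second consequences can be reported separately. Counting all films is a legitimate measure of imaging burden, but number of radiographs, radiation and costs already cover that.

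Late detection is also measured directly as a secondary outcome. This softens the consequence without correcting the primary ratio.

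**Conclusion.** The point holds as a flaw in the definition of the primary outcome and should be fixed. As written, the ratio blends surveillance yield with imaging after treatment has started. Within PE-FU it falls from 28.0% to 21.9% as detection moves from all late to all early; this range assumes 28% progressing, no false alarms, and the month-24 film still taken in treated patients. At the planned film count, the choice of denominator moves PE-FU between 23.3% and 28.0%, depending on how many extra films are true detections. It moves S-FU from 5.75% to about 6.3% (range 5.75% to 6.95%).

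These shifts are modest beside the planned contrast of 23.3 − 5.75 = 17.6 points, which comes mainly from 4 against 1.2 films per patient. The order of the arms does not reverse in any case computed, and the sample size figures are not in error on this account. What suffers is the meaning and size of the estimate. Any larger effect rests on post-treatment films that the documents do not describe.

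**What to change.** In Patient characteristics and outcome measures and in Effect evaluation primary outcome parameter, define both numerator and denominator as post-baseline radiographs up to and including the one that led to the patient's first treatment consequence, or all post-baseline radiographs to month 24 if there is none. Patients stay in follow-up and in the ITT population; only the count for this ratio stops. Keep later films in the radiation, cost and number-of-radiographs outcomes. Report the all-films ratio, with any second consequence such as surgery after a brace, as a sensitivity analysis.

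The cost is a sentence in each place. It draws on visit-level radiographs, treatment starts and the recorded reasons for non-protocolised films, and should need no new data collection. The denominator becomes slightly smaller (365.5 instead of 400 films per 100 S-FU patients with even detection), and second consequences leave the primary count.

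### A linear mixed model is assigned to a primary outcome that is yes/no per radiograph; at the planned rates its nominal 95% intervals would cover about 72% to 85%

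*Protocol article*

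**What the plan says.** Under Patient characteristics and outcome measures: "Primary outcome is defined as the proportion of radiographs that has led to treatment consequences in each subgroup". The same paragraph adds: "A treatment consequence is defined as start of brace therapy or any surgical intervention". Each radiograph therefore scores yes or no, and the subgroup figure is a ratio of radiograph counts.

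Under Effect evaluation primary outcome parameter, two methods appear:
- The first is a test on counts: "To compare the primary outcome between the PE-FU group and the S-FU group, Pearson’s chi-square test is used".
- The second is a regression model: "To evaluate the effect according to subgroups, linear mixed-effects models that account for repeated measurements will be performed". Scoliosis centre and baseline covariates enter it as adjustment terms. The section then adds: "Assumptions of linear mixed modelling will be assessed and if needed variable transformations will be performed".

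The Abstract (Methods and analyses) mentions only the second: "Outcomes will be analyzed using linear mixed-effects models, adjusted for relevant baseline covariates". The section on secondary outcome parameters also refers back to the mixed model as the one applied to the primary outcome. Logistic regression is named only there, for the preference and association analyses.

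**The concern.** A default linear mixed model assumes one residual variance for all observations. For a 0/1 outcome the variance is p(1−p), so it differs between arms whenever the rates differ. The plan expects a large difference in rates and a large imbalance in radiograph numbers, with the smaller number in the arm with the larger variance. In that configuration a pooled variance makes the standard error too small. The adjusted effect that readers will rely on would carry an interval narrower than the data support.

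Two lesser matters go with this. The chi-square test treats a patient's several radiographs as independent. And because the outcome and sample size are set per subgroup, the two methods address the same comparison, and the article does not say clearly which one decides superiority in each RCT.

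**Working it through.** **Inputs** (Appendix, sample size per subgroup; follow-up radiographs only, before dropout)

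| RCT | n per arm | S-FU rate | PE-FU rate | S-FU radiographs | PE-FU radiographs |
|---|---|---|---|---|---|
| Pre-treatment | 60 | 23%/4 = 5.75% | 28%/1.20 = 23.3% | 60 × 4 = 240 | 60 × 1.20 = 72 |
| Post-brace | 55 | 23%/4 = 5.75% | 28%/1.15 = 24.3% | 55 × 4 = 220 | 55 × 1.15 = 63.25 |
| Post-surgery | 69 | 10%/6 = 1.7% | 15%/1.05 = 14.3% | 69 × 6 = 414 | 69 × 1.05 = 72.45 |

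**Reproducing the plan's sample sizes.** n = (1.96 + 0.842)² × [p1(1−p1) + p2(1−p2)] / (p1−p2)², two-sided, gives 59.2, 54.1 and 68.4, rounded up to 60, 55 and 69. Multiplying by 1.10 gives 66, 61 and 76. The plan's figures are those of a simple unadjusted two-proportion comparison.

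**Standard error with one residual variance.** Let v = p(1−p) in each arm.
- Model SE = √[v̄(1/n1 + 1/n2)], with v̄ = (n1v1 + n2v2)/(n1 + n2).
- Arm-specific SE = √(v1/n1 + v2/n2).
- Coverage of a nominal 95% interval = 2Φ(1.96 × ratio) − 1, where ratio = model SE / arm-specific SE.

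Pre-treatment: v1 = 0.0575 × 0.9425 = 0.0542; v2 = 0.2333 × 0.7667 = 0.1789; v̄ = (240 × 0.0542 + 72 × 0.1789)/312 = 0.083. Model SE = √[0.083 × (1/240 + 1/72)] = 0.0387. Arm-specific SE = √(0.0542/240 + 0.1789/72) = 0.0521.

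| RCT | Model SE | Arm-specific SE | Ratio | Coverage |
|---|---|---|---|---|
| Pre-treatment | 0.0387 | 0.0521 | 0.743 | 85.5% |
| Post-brace | 0.0412 | 0.0562 | 0.732 | 84.9% |
| Post-surgery, 6 films per S-FU patient (414) | 0.0228 | 0.0416 | 0.549 | 71.8% |
| Post-surgery, 3 exposures per S-FU patient (69 × 3 = 207), 1.7% kept | 0.0286 | 0.0421 | 0.680 | 81.7% |

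The last row keeps the stated rate but counts visits. A per-visit rate would be 10%/3 = 3.3%, which the article does not state; it would give about 86%.

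**Does the random effect rescue the model?** If a patient has at most one consequence over four S-FU radiographs, the per-patient variance is 0.23 × 0.77 = 0.177, against 4 × 0.0542 = 0.217 under independence. The ratio is 0.82 and the within-patient correlation (0.82 − 1)/3 = −0.06. A random-intercept variance would then be estimated near zero, leaving ordinary least squares. A 10,000-run simulation of that common-variance model at the pre-treatment rates gave 85.8% coverage.

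**Linear model under equal rates.** The variances are then equal and the mechanism disappears. Simulated type I error (20,000 runs, no random effect fitted) was 4.5% pre-treatment, 4.2% post-brace and 3.8% to 4.2% post-surgery.

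**Chi-square type I error** (10,000 runs)
- At most one consequence per patient: 4.4% with planned radiograph numbers; 2.8% with four per patient in both arms.
- Assumed positive within-patient correlation of 0.05, 0.10 or 0.20: 4.9%, 5.8% or 7.0%.
- Post-surgery, both films of a biplanar pair counted as having the consequence: S-FU variance is 4 × 0.10 × 0.90 = 0.36 against 6 × 0.0333 × 0.9667 = 0.193, a design effect of 1.86; type I error is about 17%.

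**The case against.** The strongest reply is that the superiority decision is safe. Unequal variances arise only when the rates differ, and the linear model's simulated type I error is not inflated. At the planned rates the differences are about 3.4, 3.3 and 3.0 arm-specific standard errors from zero (0.1758/0.0521, 0.1860/0.0562, 0.1262/0.0416), so the expected result stays significant with the correct standard error. This stands. A reader might infer a raised risk of a false superiority claim from the linear model; the figures do not support that.

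A reader might also blame the chi-square test for intervals that are too narrow. It yields no interval, and with at most one consequence per patient its type I error is nominal or lower. Its exposure depends on how films and repeat consequences are counted.

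A further reply is that the chi-square test is evidently the deciding test: the article names it for the arm comparison, the sample sizes match an unadjusted two-proportion formula, and an analysis plan not shown may settle the rest. This stands in part, so calling these two competing primary analyses would go too far. But the Abstract names only the linear mixed model, and the secondary-outcome section treats it as the primary outcome's model. The article's own statements pull in different directions.

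The word linear is not easily read as shorthand for a generalised model either, since the transformation sentence belongs to normal-theory modelling and logistic regression is named elsewhere.

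**Conclusion.** The point holds for the model and its intervals. The article assigns a linear mixed model to a binary outcome, and transformation cannot repair that. At the plan's own rates the standard error is understated by about 26% pre-treatment and 27% post-brace, with coverage near 85%. Post-surgery coverage is about 72% on the article's own six-film count, or 82% with three exposures.

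These figures assume a single residual variance, a random-intercept variance near zero, radiograph numbers as in the Appendix and no covariates. The simulations also assume Poisson numbers of extra PE-FU radiographs; the within-patient correlations and the rule for counting biplanar pairs are assumptions that the article does not supply.

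The consequence is a misleading interval around the reported effect when the arms differ. The chi-square test's neglect of clustering is a conditional, secondary weakness, and the unclear choice of deciding analysis is a matter of inconsistent wording.

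**What to change.** For each RCT, name one deciding analysis for a binary outcome with the patient as cluster. One option is a GEE on radiographs with small-sample robust standard errors and the risk difference as the single primary effect measure. The small-sample correction is worth specifying: a small simulation (300 runs per scenario) with patient-clustered robust standard errors gave about 93% coverage.

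Keep centre adjustment sparse where events are few, for example by grouping centres. Post-surgery the plan implies about 69 × 10% + 69 × 15% ≈ 17 events, too few for many centre and minimisation terms. State whether a biplanar pair counts once or twice. Keep the chi-square test as an unadjusted sensitivity analysis. Remove the linear mixed model and the transformation sentence for this outcome, retain them for continuous secondary outcomes, and align the Abstract's description wherever it is reused.

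The cost is wording and analysis code, with no extra patients or data. Intervals become somewhat wider: at the planned pre-treatment rates by a factor of about 0.0521/0.0387 = 1.35, which is the width the data warrant.
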